### Participant timeline

5.2

Expected time of the trial will be 1 calendar year after ethical approval and will be renewed annually for 5 years.

### Sample size and recruitment

5.3

All patients will undergo static whole-body FLT PET/CT imaging at baseline in a cohort of 21 patients.

## Methods: data collection, management, and analysis

6

All enrolled patients will undergo a baseline FLT PET/CT at baseline. All PET data will be acquired on the Siemens mCT PET/CT scanner in 3D mode. FLT-PET scans will be performed in static mode 60 minutes ± 10 minutes postinjection.

Diagnostic agent [^18^F] FLT: FLT will be synthesized by the HMC Radiochemistry Facility. The target patient activity will be 10 mCi ± 10%. The product will be required to meet all of the release acceptance criteria outlined by HMC policies for purity, sterility, endotoxin, and identity before administration.

Patient preparation and administration of FLT-PET: No specific dietary restrictions or hydration are required for FLT-PET scans. However, patients will be urged to drink plenty of water before and after the PET studies. FLT will be prepared by the HMC cyclotron Core Facility and assessed for quality control following “good manufacturing practice” criteria. For each scan, patients will receive approximately up to 10 mCi ± 10% FLT by intravenous infusion.

Whole body scan:

The baseline FLT-PET study will be performed in static mode as follows: Static FLT-PET acquisition:

Scout view and low dose CT (see below) for 2 to 3 PET FOV's (∼24 cm per FOV) will be obtained.Static PET acquisition will start at 60 min ± 10 min post-injection at 3 minutes per PET field-of-view.

All studies will be carried out on a Siemens mCT PET/CT scanner residing at the PET center at HMC, and in 3D mode.

Image analysis and interpretation details:

All FLT-PET images will be reviewed and examined by a board-certified physician who is a member of the HMC PET/CT or radiology services, and who is experienced in PET interpretation. CT, attenuation-corrected PET, and fused PET-CT images will be available and reviewed simultaneously for each patient. Interpretation of the cancer site will be based on lesion SUV, facility of radiotracer uptake, and detectability.

**Bone marrow examination**: Bone marrow biopsy will be performed as a part of routine work-up for all selected patients before the FLT-PET scan. Subjects will be categorized based on their diagnosis; ET/Prefibrotic myelofibrosis vs borderline undifferentiated, and ET vs/or Prefibrotic.

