## Introduction

1

Positron emission tomography (PET) with fluorodeoxyglucose (^18^F-FDG) combined with computed tomography is a major tool for the diagnosis, staging, and monitoring of treatment response in clinical oncology.^[1]^ 3′-18Fluoro-3′-deoxy-L-thymidine (FLT) with PET is a surrogate for assessing noninvasively.^[2]^

Myeloproliferative Neoplasms (MPNs) are clonal hematopoietic stem disorders are characterized by high rate of effective proliferation of one or more cell lineage. MPNs exhibit overlapping syndromes that can progress to fibrotic stage or progress into acute leukemia. Preliminary results of a pilot study^[3]^ suggested that this technique (FLT-PET) could be useful to assess bone marrow (BM) activity and extramedullary hematopoiesis in patients with Myelofibrosis (MF).

The current standard of care approach for follow-up in patients with MF is based on pathological markers (peripheral blood counts and bone marrow histomorphology) and molecular markers. Bone marrow examination is considered as the gold standard diagnostic method in MF patients. It provides detailed information about cellularity, morphology of each lineage, the degree of fibrosis, and, transformation and dysplastic features. However, many patients are reluctant to go for this invasive technique which precludes precise assessment of disease activity at the desirable frequencies. Alternative noninvasive clinical techniques are still lacking.

In a recent study, Vercellino et al showed the feasibility of FLT-PET to evaluate the diagnostic value of this technique in in primary myelofibrosis where ^18^F-FLT PET appears to be a reliable and convenient technique to assess hematopoietic activity in bone marrow.^[4]^ Assessing the patterns of ^18^FLT uptake in the different subgroups of MPNs are still however needed. In this study protocol we propose to study and characterize FLT uptake patterns in PET images of early prefibrotic stages of PMF (pre-PMF) in different clinical and genetic settings, and Essential Thrombocythemia (ET).^[4]^ Specifically, we will assess the value of FLT-PET uptake patterns in diagnosis and treatment response assessment of PMF patients. We will also examine their feasibility to differentiate between early stage PMF and ET, and will correlate those with disease activity, degree of fibrosis, and early detection of acute transformation.

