## Objectives

2

The objective of this study is to:

Assess the value of FLT-PET uptake patterns in the diagnosis, staging, and response to therapy monitoring of malignant hematopoiesis in patients with pre-PMF and ET diseases.Identify different patterns of uptake in patients with pre-PMF and ET in different clinical settings.Compare the values of FLT-PET in disease diagnosis, assessment of disease activity, detection of transformation, monitoring of treatment response, and grading of fibrosis to those of bone marrow biopsy (gold standard) in pre-PMF and ET.Study the ability of FLT-PET to differentiate between pre-PMF and ET.Correlate FLT-PET uptake patterns with different genetic makeup (JAK2, [calreticulin] CALR, MPL, or Triple negative disease) or allele burden in patients with pre-PMF and ET.

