## Exclusion criteria

5

1.Patient not fulfilling the inclusion criteria.2.Vulnerable groups: pregnant, minors, and prisoners will be excluded.

Bone marrow will be collected as part of the routine diagnostic work-up. No extra bone marrow material will be collected solely for the aim of the study.

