### Outcomes

5.1

Primary outcome measure:

Number of patients with ≥ 50% increase in FLT uptake in the PET images compared to and at 12 months post-baseline scan in patients with PMF and ET.∘Examine the value of FLT-PET in assessing malignant hematopoiesis in patients with PMF and ET [Time Frame: 12 Months]

Secondary outcome measures:

Reduction of >50% of allele burden of different mutations (JAK-2, MPL, CALR) and its expression on FLT- PET uptake pattern 12 moths post-baseline scan.∘Correlation of different mutations (JAK-2, MPL, CALR) expression and allele burden with FLT- PET uptake patterns [Time Frame: 12 Months].

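### Objective 3 compares FLT-PET with marrow biopsy for transformation and treatment response, but the only marrow described precedes the scan and study-only marrow is excluded, so follow-up pairs would be an incomplete, selected subset

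*Protocol article*

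**What the plan says.** Section 2 (Objectives) of the protocol article lists five objectives. The third compares FLT-PET with marrow biopsy on five counts: diagnosis, disease activity and then "detection of transformation, monitoring of treatment response, and grading of fibrosis to those of bone marrow biopsy (gold standard) in pre-PMF and ET".

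Three statements govern when marrow is available:

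- Section 6 (Methods: data collection, management, and analysis), under bone marrow examination: "Bone marrow biopsy will be performed as a part of routine work-up for all selected patients before the FLT-PET scan".
- Section 5 (Exclusion criteria): "Bone marrow will be collected as part of the routine diagnostic work-up", and then "No extra bone marrow material will be collected solely for the aim of the study".
- Section 1 (Introduction) counts marrow histomorphology among the markers used in standard follow-up of myelofibrosis, but adds that "many patients are reluctant to go for this invasive technique which precludes precise assessment of disease activity at the desirable frequencies".

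On the imaging side, section 6 describes one acquisition: "All enrolled patients will undergo a baseline FLT PET/CT at baseline". Section 5.1 (Outcomes) measures uptake change "at 12 months post-baseline scan in patients with PMF and ET". Section 5.3 gives the size: "in a cohort of 21 patients".

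**The concern.** A marrow taken before a scan can serve as reference for what the patient has at that time: diagnosis, fibrosis grade, disease activity. It cannot serve as reference for a response or transformation that comes later. For those two counts the objective needs a marrow result after baseline. The document describes none and states that none will be taken for the study alone.

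This is separate from how the 12-month scan is described. If every patient had that scan, there would still be no described marrow result to set beside it.

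At stake is the kind of claim the trial could make. Section 6.2 speaks of choosing parameters that predict response and of reporting sensitivity, specificity and predictive values. If marrow is the reference for response, as objective 3 implies, those figures would come from whichever patients happened to have a repeat marrow. A statement that FLT-PET monitors response or detects transformation as well as biopsy would then have no representative set of pairs behind it.

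**Working it through.** The 21 in section 5.3 comes without effect size, power or precision target, so there is no stated figure to reproduce. The check sets the passages side by side and then illustrates the scale.

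**1. Which comparisons have both tests described?**

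| Comparison in objective 3 | Marrow needed | Marrow described |
|---|---|---|
| Diagnosis | around the baseline scan | yes, all selected patients |
| Disease activity at baseline | around the baseline scan | yes |
| Fibrosis grade at baseline | around the baseline scan | yes |
| Treatment response | after baseline | none |
| Transformation | after baseline | none |

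Described pairs at baseline: 21 of 21. Described pairs after baseline: 0 of 21. The zero counts what the article describes; it does not forecast how many marrows routine care will produce.

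**2. Precision if only some patients have a follow-up marrow.** The share is not given. I assume 20%, 30%, 50% and 100% of 21, that is 4.2, 6.3, 10.5 and 21, taken as 4, 6, 10 and 21 patients. Observed agreement is set as near 80% as whole patients allow. The exact (Clopper-Pearson) limits for x of n are the 0.025 quantile of Beta(x, n − x + 1) and the 0.975 quantile of Beta(x + 1, n − x).

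| Patients with a pair | Agree | 95% interval | Width |
|---|---|---|---|
| 4 | 3 (75%) | 19% to 99% | 0.80 |
| 6 | 5 (83%) | 36% to 100% | 0.64 |
| 10 | 8 (80%) | 44% to 98% | 0.53 |
| 21 | 17 (81%) | 58% to 95% | 0.37 |

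**3. Number of transformations.** The document gives no rate. For an assumed yearly rate p, expected events are p times patient-years, and the chance of none is (1 − p) raised to the number of patient-years.

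- Twelve months each, 21 patient-years: at 1%, 0.21 events and 0.99^21 = 81% chance of none; at 3%, 0.63 events and 0.97^21 = 53%.
- Upper bound if all 21 were followed for the five years that section 5.2 allows by annual renewal, 21 × 5 = 105 patient-years: at 1%, 1.05 events and 0.99^105 = 35%; at 3%, 3.15 events and 0.97^105 = 4%.

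Even the upper bound yields about one to three events at these rates, before asking how many of those patients have a marrow close to a scan.

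**4. Direction of bias.** Let v1 and v0 be the shares of PET-positive and PET-negative patients who get a follow-up marrow, with marrow depending on the PET result alone. Among those with marrow, apparent sensitivity is Se·v1 / (Se·v1 + (1 − Se)·v0), and apparent specificity is Sp·v0 / (Sp·v0 + (1 − Sp)·v1). If v1 exceeds v0, sensitivity is overstated and specificity understated; if they are equal, neither is biased. If marrow follows clinical suspicion rather than the PET result, the issue is instead spectrum: the patients measured do not represent the cohort, and the document does not fix the direction.

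**The case against.** The strongest reply is that routine care may supply the missing marrow. The Introduction places marrow histomorphology in standard myelofibrosis follow-up, the abstract calls biopsy standard of care, and the exclusion section bars only material taken solely for the study. This stands in part. A reader might infer that no marrow will exist after baseline, and the document does not support that. Yet the same paragraph of the Introduction says reluctance keeps biopsy from being done as often as wanted, and nothing describes follow-up marrow in ET. Some later marrow is possible; complete or representative coverage is not indicated.

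Second, section 6 says the biopsy precedes the FLT-PET scan without naming the baseline scan. Baseline is the natural reading, since it is the only acquisition described and the marrow belongs to diagnostic work-up, but it is a reading.

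Third, a journal article condenses, and a visit schedule may sit in the full protocol. That would answer a complaint about a missing schedule. Here, however, the article states when and why marrow is taken and what is excluded, and that rule does not fit an objective it also states.

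Fourth, a reader might infer that specificity could not be estimated at all, or that sensitivity is bound to be overstated. Neither follows. Patients re-biopsied on suspicion and found not to have transformed are reference negatives, so specificity could be computed, though imprecisely and in an unrepresentative group. Overstated sensitivity requires repeat marrow to be linked to the PET result, which the document does not say.

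Finally, the section 5.1 outcomes do not depend on a follow-up marrow, and section 6.2 centres on telling pre-PMF from ET. That is correct and limits the reach of the point.

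**Conclusion.** The point holds as a conflict between objective 3 and the marrow rules in sections 5 and 6. Two of the five comparisons, transformation and treatment response, have no described reference result after baseline. Follow-up pairs would be an incomplete subset selected by clinical need or willingness, and accuracy estimates from them would be imprecise and open to verification and spectrum bias.

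The number of such pairs is unknown. The 20% to 50% shares and the 1% to 3% yearly rates are illustrations, not figures from the document, and the conclusion does not depend on them. It rests on the stated timing of marrow, the exclusion of study-only marrow and the longitudinal nature of the two comparisons.

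The baseline comparisons and the section 5.1 outcomes are untouched. Nor does it follow that the two aims must be deleted: they can stay if they are described as what the data can support.

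**What to change.** Reconcile section 2 (objective 3), section 5 (marrow collection) and section 6 (bone marrow examination) as follows:

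- Limit the formal PET-versus-biopsy comparison, including sensitivity, specificity and cutoffs, to baseline diagnosis, disease activity and fibrosis grade, where all patients are described as having both tests.
- Label the transformation and treatment-response comparisons with biopsy as descriptive.
- Report any follow-up marrow from routine care case by case, with the number of patients out of 21 who have one. Compute no sensitivity or specificity from these, and claim no equivalence to biopsy.

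The cost is a wording amendment to the objectives and analysis text, best made before the data are analysed. Two parts of objective 3 become descriptive. No extra biopsy is needed, and the primary and secondary outcomes stay as they are.

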### Data management

6.1

Clinical, pathological, radiological, and molecular data will be compiled in data excel sheet. The clinical, pathological, and genetic data will be correlated to the FLT-PET uptake patterns.

A senior PET/CT technologist who is already involved in research will be assigned to the study. The responsibilities of the designated person include project compliance, data collection, abstraction and entry, data reporting, regulatory monitoring, problem resolution and prioritization, and coordination of the activities of the protocol study team.

The data collected for this study will be transferred to a secure database managed by the HMC IT team (eg, PACS). All data generated in this study will be the property of HMC. Original data acquired on the PET/CT scanner console will be managed as per the PET/CT center policy and procedures regulations.

Source documentation will be available to support the computerized patient record. Study personnel will record clinical data in each patient's source documents (ie, the patient's medical record). The study team will maintain adequate and accurate records to enable the conduct of the study to be fully documented and the study data to be subsequently verified. After study closure, the investigators will maintain all source documents, study-related documents, and the data stored in the database used for data collection. Data will be entered throughout the duration of the trial as patients are enrolled.

Clinical, pathological, radiological, and molecular data will be compiled in data excel sheet. The clinical, pathological and genetic data will be correlated to uptake pattern of FLT-PET.

A senior PET/CT technologist who is already involved in research will be assigned to the study. The responsibilities of the designated person include project compliance, data collection, abstraction and entry, data reporting, regulatory monitoring, problem resolution and prioritization, and coordinate the activities of the protocol study team.

The data collected for this study will be transferred to a secure database managed by the HMC IT team (eg, PACS). All data generated in this study will be the property of HMC. Original data acquired on the PET/CT scanner console will be destroyed as per the PET/CT center policy and procedures regulations.

Source documentation will be available to support the computerized patient record. Study personnel will record clinical data in each patient's source documents (ie, the patient's medical record). The study team will maintain adequate and accurate records to enable the conduct of the study to be fully documented and the study data to be subsequently verified. After study closure, the investigator will maintain all source documents, study-related documents, and the data stored in the database used for data collection. Data will be entered throughout the duration of the trial as patients are enrolled.

### Statistical methods

6.2

The primary aim is to study the ability of FLT-PET in differentiating between pre-PMF and ET. The focus of the data analysis in our study is to determine the predictive value and accuracy of FLT-PET uptake in predicting diagnosis. For this purpose, we will use receiver-operating-characteristic (ROC) curves and will compute areas under curves for each parameter for its robustness in predicting diagnosis. In addition, we will create a model probability cutoff graph to choose parameters that best predict response and determine cutoffs that showed highest accuracy (sensitivity, specificity, positive, and negative predictive values of these parameters). The ROC curves provide a comprehensive and visually attractive way to summarize the accuracy of predictions. The ROC curve shows the tradeoff between sensitivity and specificity and is a better method to detect the performance of a developed test. Kruskal-Wallis will be also used in addition or to replace ROC curves depending on the final number of recruited patients and statistical conditions. A 2-sided *P* value <0.05 will be considered to be statistically significant. All statistical analyses will be done using MedCalc (Medcalc Software, Ostend, Belgium).

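### Choosing the best uptake parameters and the highest-accuracy cutoffs in the same 21 patients will overstate FLT-PET's accuracy; 7 to 25 points on average under plausible assumptions

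*Protocol article*

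**What the plan says.** Section 6.2 of the protocol article sets the target: "The primary aim is to study the ability of FLT-PET in differentiating between pre-PMF and ET". It then says the analysis "will compute areas under curves for each parameter for its robustness in predicting diagnosis". Next, a graph of model probability cutoffs will be used to "choose parameters that best predict response and determine cutoffs that showed highest accuracy (sensitivity, specificity, positive, and negative predictive values of these parameters". One general significance rule applies, a two-sided P "value <0.05 will be considered to be statistically significant".

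Section 5.3 gives the data for all of this: "All patients will undergo static whole-body FLT PET/CT imaging at baseline in a cohort of 21 patients". The article describes no second group of patients. It does not say how many uptake parameters will be screened or how the 21 divide between pre-PMF and ET. The bone marrow paragraph in section 6 also has a borderline, undifferentiated category, so fewer than 21 may enter a pre-PMF versus ET comparison.

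The selection sentence speaks of predicting response, while the sentences before it speak of predicting diagnosis.

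**The concern.** The rule makes two data-driven choices, which parameters look best and which cutoff looks best, and reports performance at those choices. If the same patients serve for choosing and for reporting, the figure is a maximum over many candidates. A maximum of noisy estimates lies above the true value on average. With about ten patients per diagnosis, each patient is worth roughly five accuracy points (1/21 = 4.8), so the noise being maximised over is large.

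This matters because section 6.2 makes the predictive value and accuracy of FLT-PET the focus of its analysis. A reader could take an apparent accuracy in the high eighties as evidence that FLT-PET separates pre-PMF from ET, when the same rule in new patients would do much less well, or when the parameter carries no information at all.

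**Working it through.** **No figure to reproduce.** The 21 is stated without a target AUC, precision or power, and the article gives no expected accuracy. The check is therefore a simulation on declared assumptions.

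**Inputs**
- From the article: N = 21, more than one parameter, selection by best prediction, cutoff by highest accuracy.
- Assumed: k = 1, 3, 5 or 10 parameters; split 11/10 or 14/7; normal values with equal variance; true AUC 0.5 (noise), 0.7, 0.8 or 0.9; correlation between parameters 0 or 0.5.

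**Steps (1,500 to 3,000 runs per setting)**
1. Compute the AUC of each parameter, with direction free, and keep the largest.
2. Choose the cutoff that maximises accuracy. Maximising the Youden index was also tried.
3. Overestimate = accuracy in the 21 patients minus accuracy of the same parameter and cutoff in new patients with the same mix.

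**Apparent against new-patient accuracy, 11/10 split, independent parameters, accuracy-maximising cutoff**

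| k | All noise | All AUC 0.8 | All AUC 0.9 |
|---|---|---|---|
| 1 | 67% vs 50% | 79% vs 70% | 87% vs 80% |
| 3 | 71% vs 50% | 86% vs 71% | 92% vs 80% |
| 5 | 73% vs 50% | 87% vs 71% | 94% vs 80% |
| 10 | 75% vs 50% | 90% vs 71% | 96% vs 80% |

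**Mean overestimate in percentage points, over both splits, both correlations and both cutoff rules**
- One informative parameter, cutoff choice only: 7 to 8 (AUC 0.9), 9 to 10 (AUC 0.8), 9 to 12 (AUC 0.7).
- Best of 3 to 10 equally informative parameters: 11 to 16, 12 to 19 and 13 to 21 for the same AUCs.
- One informative parameter among noise parameters: 8 to 9, 11 to 16 and 14 to 22.
- Noise only: 11 to 17 with one parameter, 16 to 25 with 3 to 10.

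The Youden index (sensitivity + specificity − 1) is overstated by about twice as much in a near-even split. For example, five parameters at AUC 0.8 give 0.33 for the index against 0.16 for accuracy.

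**Good-looking AUC from noise.** One noise parameter shows an AUC of at least 0.70 in 13 to 16% of studies. For five independent ones, 1 − (1 − q)^5 gives 1 − 0.87^5 = 50% at q = 0.13 and 1 − 0.84^5 = 58% at q = 0.16. Simulated directly, the figure is 42 to 56%; the lower part of that range comes from correlation 0.5. An AUC of at least 0.80 appears in 8 to 12%.

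**Predictive values.** PPV = se·p / [se·p + (1 − sp)(1 − p)], with p the pre-PMF share. Illustrating with se = sp = 0.80:
- p = 0.20: 0.16 / (0.16 + 0.16) = 0.50
- p = 0.80: 0.64 / (0.64 + 0.04) = 0.94

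The test is the same in both cases; only the enrolled mix differs.

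**The case against.** The strongest reply is that this is a phase I, single-group study in which proposing candidate cutoffs is ordinary, that no section says a cutoff will guide care, and that a condensed article may leave validation and multiplicity to a full protocol or SAP that is not shown. Much of this stands. The absence of a stated correction or named primary parameter is not itself a fault here, and a reader should not infer that none is planned. The point rests only on the selection rule that section 6.2 does state. That section does not call the result exploratory: it declares a primary aim, a significance threshold and predictive values.

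Three stronger readings are tempting and not supported:
- **That accuracy will come out about 10 points too high.** This fits one parameter of moderate strength with only the cutoff optimised (at AUC 0.75 and a 10/11 split, 76% apparent against 66% true). The article fixes none of those inputs, and choosing among several parameters usually adds more.
- **That the chosen cutoff will fail in new patients.** In that same setting the best attainable accuracy is Φ(0.954/2) = 68.3%, so the selected cutoff, at 66%, loses only about 2 points. What does not carry over is mainly the reported accuracy.
- **That each parameter is tested at 0.05, with a known familywise error.** Section 6.2 gives one general threshold and says AUCs will be computed; it does not say each is tested against 0.5.

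It is also fair to say that section 5.1 names a different primary outcome, a 12-month change in uptake. Accuracy is thus the declared primary aim of section 6.2, not undisputedly of the whole trial.

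**Conclusion.** The concern holds in this form. As written, the rule selects parameters and cutoffs for best performance, and the article describes no patients beyond the 21 in whom to evaluate them, so the accuracy figures will be biased upward. The direction was the same in every setting tried. The size, about 7 to 25 percentage points of overall accuracy on average, depends on the assumed number of parameters, true AUC and split, and should be quoted only with those assumptions. It was worked out for overall accuracy and the Youden index; how it divides between sensitivity and specificity depends on the split and the cutoff rule. A respectable AUC arising from noise is a realistic possibility if several parameters are screened. Separately, sample PPV and NPV would reflect the enrolled ratio of pre-PMF to ET, which the article does not fix.

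**What to change.** In section 6.2, before any analysis:
- Name one primary uptake parameter. Label the other parameters, and any cutoff derived from the data, exploratory.
- Report accuracy with bootstrap optimism correction or leave-one-out cross-validation, repeating both the parameter choice and the cutoff choice in every resample. Show corrected values beside apparent ones, with confidence intervals.
- Replace sample PPV and NPV with likelihood ratios, or give them at stated prevalences.
- State whether the cutoff rule is meant to predict diagnosis or response, and use one term throughout.

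If a full protocol or SAP already contains these steps, citing it in section 6.2 is enough.

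The cost is a few sentences and a little code, which can be run outside the named package. No extra patients or scans are needed. The price is less favourable accuracy figures. The parameter has to be named before the data are analysed, because naming it afterwards would not be credible.
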